# Shenhuang granule in the treatment of severe coronavirus disease 2019 (COVID-19): study protocol for an open-label randomized controlled clinical trial

**DOI:** 10.1186/s13063-020-04498-6

**Published:** 2020-06-24

**Keywords:** Severe COVID-19, Shenhuang granule, “Truncation and Reversion” strategy, Randomized controlled trial

## Abstract

**Background:**

Currently, coronavirus disease 2019 (COVID-19) is continuously and rapidly circulating, causing heavy damage on public health. No effective antiviral treatment has been proved thus far. Traditional Chinese medicine (TCM) has been widely applied in the treatment of a variety of infection diseases in China, hoping to produce clinical effects and reduce the use of antibiotics and glucocorticoid. The aim of this study is to evaluate the efficacy and safety of Shenhuang granule in treatment of severe COVID-19.

**Methods/design:**

This multicenter, open-label randomized controlled trial is conducted in 160 participants with severe COVID-19. The participants will be randomly (1:1) divided into treatment group or control group. All participants are given standard therapy at the same time. The experiment will receive Shenhuang granule treatment twice a day for 14 days. The clinical indicators of patients will be assessed at baseline and at 3, 5, 7, and 14 days after treatment initiation. The primary outcome is 14-day clinical outcome. Adverse events will be monitored throughout the trial.

**Discussion:**

This will be the first randomized controlled trial, which evaluate the effect of Shenhuang granule in patients with severe COVID-19 in China. The results of this trial may not only provide evidence-based recommendations to clinicians to treat severe COVID-19, but also enrich the theory and practice of TCM in treating infectious diseases.

**Trial registration:**

Chinese Clinical Trial Registry, ChiCTR2000029777. Registered on 13 February 2020.

## Introduction

In December 2019, an outbreak of unexplained pneumonia has been diagnosed in Wuhan, Hubei Province, in China, with an epidemiological link to seafood and wet animal wholesale market where there was also sale of live animals [1, 2]. The Chinese scientists isolated an unknown coronavirus from the patient’s respiratory epithelial cells of patients and performed genome sequencing of the virus [3]. Now, this new virus is named “severe acute respiratory syndrome coronavirus 2 (SARS-CoV-2),” and it causes “coronavirus disease 2019 (COVID-19).” Although COVID-19 is considered to be the origin of zoonotic diseases, human-to human transmission has been occurred [4]. It initially erupted in Wuhan and later spread to all parts of the world, resulting in 2,954,222 confirmed cases, including 202,597 deaths globally as 28 April 2020, which caused a global health emergency [5].

The COVID-19 belongs to the family Coronaviridae and order Nidovirales, and is detected in bats, with similarity in clinical features and genetic sequence to SARS-CoV [3, 6]. Many patients of COVID-19 suffer from fever, fatigue, cough, chest tightness, and dyspnea and some progress to sepsis or septic shock or died of the infection [7]. The diagnosis of new cases includes clinical characteristics, the epidemiological history, and laboratory test according to the “Guidelines for the Diagnosis and Treatment of Novel Coronavirus (COVID-19) Infection by the National Health Commission (Trial Version 7)” [8]. Currently, there is no vaccine or specific antiviral drugs for the infection except meticulous supportive care [9].

TCM, as an important part of complementary and alternative medicine, has been widely applied in preventing and treatment of epidemic disease in China for hundreds of years. Patients with severe COVID-19 often develop into sepsis or septic shock [7]. Severe COVID-19 belongs to the “epidemic febrile disease” in TCM, and the basic pathogenesis is pathogenic toxin and blood stasis. Additionally, severe COVID-19 has some characters of “the acute deficiency syndrome.” As an innovation theory, it refers to the pathological state with a rapid consumption of the vital Qi in the human body, caused by acute and severe pathological factors such as plague, poisoning, hemorrhage, loss of fluid, and all kinds of trauma [10, 11]. Based on TCM characteristic theory “six hollow organs must keep its unobstructed” and “acute deficiency syndrome,” our team put forward “Truncation and Reversion” strategy [12], and the principle on TCM for emergency, “Treating the primary (ben) for emergency cases” [10], timely controlling the course of disease and reverse disease. On the foundation of the above theories, we developed the Shenhuang granule, a formula which is composed of six medicinal herbs, including *Panax ginseng* (*Renshen*), *Rheum palmatum L.* stem (*Dahuang*), *Sargentodoxa cuneate* (*Hongteng*), *Taraxacum mongolicum* (*Pugongying*), *Aconiti Lateralis Radix Praeparata* (*Fuzi*), and Whitmania pigra Whitman (*Shuizhi*). Rhubarb is considered a purgative and bactericidal agent to reduce heat and promote blood circulation and resolve dampness [13]. *Sargentodoxa cuneate* and *Taraxacum mongolicum* have the same function of clearing heat and detoxifying, activating blood, and removing wind and relieving pain [14, 15]. Our previous studies have demonstrated that Jinhong Decoction, composed of *Rheum palmatum L*. stem, *Sargentodoxa cuneata*, and *Taraxacum mongolicum*, can inhibit the levels of TNF-α, IL-6, IL-8, and other inflammatory cytokines, protect against excessive inflammatory response, and maintain organism’s balance between inflammation and anti-inflammatory in severe infectious diseases [16, 17]. Ginseng has the functions to strongly tonify the Qi, nourishing lungs and spleen, promoting the secretion of saliva and quenching thirst, strengthening the heart, and calming the mind [18]. Several studies recently report that ginseng can directly kill bacteria and regulate bacterial adhesion, inflammation, cytotoxicity, and hemagglutination [19]. Wang et al. [20] report that ginseng extracts can inhibit different strains of influenza viruses. *Aconiti Lateralis Radix Praeparata* is considered an effective stimulant for the spleen and kidneys [21]. Recent studies report that aconite had antibacterial activity, especially against *S*. *aureus* and *E*. *coli*, as well as immunoregulation efficacy [22, 23]. Whitmania pigra Whitman has functions of breaking stagnant and eliminating blood stasis. Yao et al. [24] believe that Whitmania pigra Whitman extract effectively reduces deep vein thrombosis by inhibiting inflammation via modulating silent information regulator 1 (SIRT1)/nuclear factor-κB (NF-κB) signaling pathway. Therefore, according to the theory of TCM and modern Western medical research, Shenhuang granule should have beneficial and curative effects on severe COVID-19 [11, 12, 25].

We design this study as a multicenter, randomized, and controlled clinical trial based on the “Truncation and Reversion” strategy of TCM innovation theory and “acute deficiency syndrome.” The aim of this clinical trial is to confirm the effectiveness and safety of Shenhuang granule in blocking the deterioration of severe COVID-19 and provide reliable evidence for clinical research.

## Methods/design

### Study design and settings

The study will be a randomized, controlled, multicenter trial conducted at 4 medical centers, selected by the coordination center. The coordinating center comprise clinical experts, statisticians, and quality control experts, who will be responsible for clinical research methodology and resolving the key issues in the progress of research implementation. And they also have the responsibilities, including the design of the clinical research trial, selection of the cooperative hospitals, and provision of training courses including instructions manuals. The medical centers enrolled in this study are the Huangshi Hospital of Traditional Chinese Medicine, Tongji Hospital Tongji Medical College Huazhong University of Science and Technology, LaoHeKou Tradiational Chinese Medicine Hospital, and Leishenshan Hospital of Wuhan. A total of 160 patients that meet the eligibility criteria will be randomized into two groups (treatment group and control group) at a ratio of 1:1. The study flowchart is illustrated in Fig. 1. The Standard Protocol Items Recommendations for Interventional Trials (SPIRIT) checklist is presented in Additional file 1.

**Fig. 1 Fig1:**
[figure not shown]
Flow chart of the study design. COVID-19, coronavirus disease 2019; SOFA score, Sequential Organ Failure Assessment score; CT, computed tomography

### Objectives

The primary objectives of this trial are to evaluate the efficacy and safety of Shenhuang granule in patients with severe COVID-19.

### Population

Participant recruitment takes place daily by the study personnel from the 4 study sites in China. Subjects who meet the inclusion criteria and sign the informed consent forms will enter the screening period. Patients who meet the exclusion criteria will be excluded before randomization. The recruitment duration will last for 4 months, from February 2020 to June 2020.

### Inclusion criteria

Subjects must meet all the following requirements:
Hospitalized patients with 2019 novel coronavirus confirmed by SARS-CoV-2 nucleic acid testing of the respiratory specimens which showed positive results by means of real-time reverse transcription polymerase chain reaction (RT-PCR) assay.Meet any one of the criteria for severe type:Respiratory distress: RR ≥ 30/minBlood oxygen saturation of resting state ≤ 93%Arterial oxygen partial pressure (PaO_2_)/fraction of inspiration O2(FiO_2_)(P/F) ≤ 300 mmHgBe 18–80 years of ageProvide signed informed consent form

### Exclusion criteria

The exclusion criteria are as follows:
Pregnant and lactating womenAllergic to one or more substance in “Shenhuang granule”Severe primary disease including malignant tumor, blood diseases, HIV, and severe liver and kidney dysfunctionsObstructive pneumonia, interstitial pulmonary fibrosis, alveolar proteinosis, and hypersensitivity pneumonitis caused by obstructive lung tumors

### Patient withdrawal

The rejection and withdrawal criteria are as follows:
Adverse events and complications occur, and the investigator considers that it is necessary to terminate the trialVoluntary withdrawalThose who are lost follow-up

In patient withdrawal, all study interventions will cease. All data captured up to this point in time is stored in the database, and safety-related data are documented until day 14 if possible. Data from such patients become the dataset for efficacy and safety analysis on day 14.

### Monitoring of compliance

The methods to improve the compliance of researchers mainly include the following: (1) selecting researchers carefully and rigorously, (2) strict and comprehensive training and assessment, (3) streamlining the research process, (4) strengthen communication and supervision, and (5) appropriate incentives. In this study, the subjects are seriously ill. There is no specific medicine for this disease, and the patients have relatively high compliance with TCM.

However, the following aspects still need to be strengthened by the investigator’s control of the subject’s compliance: (1) the researcher who talks with the patient or their legal agents for informed consent should have strong communication skills and rich clinical experience, be able to communicate with empathy, and answer patients’ questions to obtain full understanding and trust, so as to avoid non-compliance after enrollment and (2) subjects should maintain necessary contact after being transferred or discharged from the hospital after the end of the drug treatment period.

### Sample size

A previous study [26] on COVID-19 by traditional Chinese medicine showed that the clinical cure rate in the conventional treatment group was 61.11%, while it was 91.18% in the group receiving traditional Chinese medicine plus routine treatment. According to the literature, presuming that the rate of the clinical effective rate in the treatment group is improved from 61.11 to 91.18%, the sample size is calculated according to the parameters *α* = 0.05 (two-sided test) and *β* = 0.1. Comparing the rates of the two groups with respect to the sample size estimation formula, we calculated that 41 patients should be recruited in each group. Studies with a similar patient population have the drop-out rate of 10% [27], and we will enroll a total sample size of 160 participants. We used the calculation tool on https://www.cnstat.org/samplesize/.

### Randomization, allocation concealment, and blinding

The randomization sequence is generated by SPSS 19.0, using permuted small blocks of random size, stratified by medical center, and grouping the Chinese medicine group and the control group on a 1:1 schedule. The two sets of allocation codes are kept in opaque envelopes; one set is kept by the research sponsor and the other set by the pharmacy administrators, who then assign the study drug to the nurses for administration. This is an open-label study. The allocation concealment is blinded before the envelop is opened. After randomization, subjects randomized to the intervention arm will be receiving combined Shenhuang granule and Western medicine therapy, or only Western medicine therapy. The evaluators and statistician will be blinded until the completion of the visit and analysis. The statistical analysis is carried out by the professors of statistics at the Shanghai University of Traditional Chinese Medicine.

### Interventions

The Shenhuang granule comprises 50 g of *Panax ginseng C. A. Mey*, 40 g of *Rheum palmatum L.* stem, 30 g of *Sargentodoxa cuneata* stem, 30 g of *Taraxacum mongolicum*, 50 g of *Aconiti Lateralis Radix Praeparata*, and 6 g of Whitmania pigra Whitman, which are packaged into two sachets. Patients in both groups can retain standard care according to the “Guidelines for the Diagnosis and Treatment of Novel Coronavirus (COVID-19) Infection (Trial Version 7)” by the National Health Commission [8]. The treatment group will be given standard Western medicine therapy and Shenhuang granule (oral, two sachets per day) for 14 days, while the control group only receives standard Western medicine therapy for 14 days. The routine care should include early fluid resuscitation, antimicrobial anticoagulants, nutritional support, and other treatments. The Shenhuang granule is provided and manufactured by the Beijing Tcmages Pharmaceutical Co., LTD (Number: Jing 20180032). Both groups then undergo a 14-day treatment. The use of all medication information is documented in the case report form (CRF).

### Outcomes and measurements

The primary outcome is clinical improvement up to 14 days after treatment. The definition of clinical improvement is that the patient’s admission status drops by 1 point on the 6-point scale or is discharged from the hospital, whichever comes first. The 6-point ordinal scale based on the well-defined WHO severity scale is as follows: 6 = death; 5 = critical, meet any of the following conditions: (1) respiratory failure, mechanical ventilation is required, (2) shock, (3) with other organ failure which requires ICU care; 4 = severe, meet any of the following criteria: (1) respiratory distress (≥ 30 breaths/ min), (2) oxygen saturation at rest ≤ 93%, and (3) arterial partial pressure of oxygen (PaO_2_)/fraction of inspired oxygen (FiO_2_) ≦ 300 mmHg; 3 = moderate, fever and respiratory symptoms, accompanied by radiological findings of pneumonia; 2 = mild, mild clinical symptoms, and no imaging signs of pneumonia; and 1 = discharged alive, (1) body temperature returned to normal for more than 3 days, (2) respiratory symptoms improved markedly, (3) pulmonary imaging showed obvious absorption of inflammation, and (4) the nucleic acid test of respiratory tract specimen is negative for 2 consecutive times.

Secondary outcomes are the mortality and rate of receiving invasive ventilator in the severe category, the improvement of oxygen saturation, and Acute Physiology and Chronic Health Evaluation (APACHE-II) score.

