### Statistical analysis

No interim analysis or subgroup analyses are planned for this trial. Full analysis set (FAS), per-protocol set (PPS), and safety analysis set (SS) will be conducted. FAS refers to the ideal set of eliminating of all subjects in a minimum and reasonable manner, according to the principle of intention-to-treat (ITT). PPS is a subset of ITT’s dataset, which has completed relevant observation according to the program requirements. The compliance of these subjects ranges from 80 to 120%, in which the subjects do not seriously violate the research program, complete all visits and CRF filling, and do not miss the main evaluation indexes and most other evaluation indexes. SS refers to all subjects who receive at least one treatment after randomization. All safety information records of subjects will be evaluated, including adverse events, severe adverse events, and clinically significant changes in safety indicators. The statistical analysis is performed in a blinded manner using the SPSS 20.0 software. For the continuous variables, the chi-squared test or Fisher’s exact test is used to compare the clinical improvement, oxygen saturation, and Acute Physiology and Chronic Health Evaluation (APACHE-II) score. Relative risk, risk difference, and number of treatments are reported with a 95% confidence interval. For the two categorical variables, we make comparison between groups and calculate the 95% CI using chi-squared tests. For the repeated measures data, category variance outcomes are analyzed using generalized estimating equations, and conclusions are drawn according to the estimating of parameter and standard error.

Our approach is to use the final observation status when no mortality is observed for 14 days, to ensure that we do not lose data about the primary outcome and the key secondary outcome. A *P* value < 0.05 is considered as statistically significant.

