This trial is designed as a multicenter, open-label randomized and controlled clinical study from the perspective of evidence-based medicine and is considered to be the most definitive research method of treatment evaluation of Shenhuang granule. In this trial, we select the 14-day clinical improvement as the primary outcome. The 14-day clinical improvement directly reflects the condition of severe COVID-19 patients and the efficacy of TCM treatment. The secondary outcomes of this trial include the mortality and rate of receiving invasive ventilator in the severe category, the improvement of oxygen saturation, and Acute Physiology and Chronic Health Evaluation (APACHE-II) score. The selected indicators in this study are used to reflect the condition of patients and to evaluate the effectiveness and safety of Shenhuang granule.

We hope this study could further explain the scientific connotation of the treatment of severe COVID-19 based on TCM innovation theory “Truncation and Reversion” strategy and “acute deficiency syndrome,” and open up new ideas and methods for clinical exploration of prevention strategy, TCM, and integrated medicine diagnosis and therapy of COVID-19. Nevertheless, the design of the trial also has potential limitations. The impact of some of the end points, such as a long-term mortality, has not yet been analyzed.

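### The primary outcome is met by a first one-point drop at any time up to day 14, with no rule for later worsening or death, so an early improver who is critical or dead on day 14 meets the definition as written

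*Protocol article*

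**What the plan says.** The definition is in the protocol article under Outcomes and measurements: "The primary outcome is clinical improvement up to 14 days after treatment". Improvement means that "the patient’s admission status drops by 1 point on the 6-point scale or is discharged from the hospital, whichever comes first". The two worst levels of the scale are given as "6 = death; 5 = critical, meet any of the following conditions", but the section does not say whether reaching either of them cancels an improvement already recorded. Mortality and invasive ventilation appear only as secondary outcomes.

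The Abstract (Methods/design) has patients "assessed at baseline and at 3, 5, 7, and 14 days after treatment initiation", and describes the endpoint as follows: "The primary outcome is 14-day clinical outcome". Statistical analysis names a chi-squared or Fisher's exact test for clinical improvement, with relative risk and risk difference. It adds: "Our approach is to use the final observation status when no mortality is observed for 14 days", and gives as the reason that data on the primary and key secondary outcomes should not be lost. The Discussion says "we select the 14-day clinical improvement as the primary outcome" and that "The 14-day clinical improvement directly reflects the condition of severe COVID-19 patients and the efficacy of TCM treatment".

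The end of the Introduction gives the aim: to confirm that the granule is effective and safe in stopping severe COVID-19 from deteriorating.

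**The concern.** The definition under Outcomes and measurements is a first-event definition. Once a patient has dropped one level at any visit, the condition is satisfied, and the text provides nothing to reverse it. A first-improvement endpoint can be sound when it is analysed as time to event with a stated rule for death. Here the timing is discarded: the test is binary, so a patient who improves on day 3 and then dies counts the same as one who improves and stays well.

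That fits poorly with the trial's aim. An arm with brief early gains and later deterioration could do well on the primary test. The Abstract and Statistical analysis also leave room for a different endpoint, status at day 14, so the same data could be scored in two ways. In an open-label trial, that choice should be fixed before anyone sees the results.

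**Working it through.** **1. Scoring the same patient under each statement.** Assume admission at level 4 (severe).

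| Course | Outcomes and measurements (first drop by day 14) | Statistical analysis, if read as a scoring rule (final status) |
|---|---|---|
| 4, then 3 on day 3, still 3 on day 14 | improved | improved |
| 4, then 3 on day 3, 5 on day 14 | improved | not improved |
| 4, then 3 on day 3, dead (6) by day 14 | improved | not stated: the sentence covers only patients without a death |
| 4 throughout | not improved | not improved |

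The definitions part company in rows two and three, which are the patients whose disease deteriorated after an early gain.

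**2. The plan's own sample size.** Inputs from Sample size: control 61.11%, treatment 91.18%, two-sided alpha 0.05, power 90%. With p̄ = (0.6111 + 0.9118)/2 = 0.7615:

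n = [1.960·√(2p̄(1−p̄)) + 1.282·√(p1(1−p1) + p2(1−p2))]² / (p2−p1)²

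= [1.960 × 0.6027 + 1.282 × 0.5640]² / 0.3007² = 40.1, rounded up to 41 per group. The stated 41 is reproduced, so the planning inputs are understood correctly.

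**3. How far the two endpoints could differ.** The documents do not say what share of improvers relapses. For illustration, treat 61.11% and 91.18% as rates of ever improving, and let a share r of improvers no longer be improved at day 14. The day-14 rate is then p(1−r). Power at 80 per group (160 randomised 1:1, no drop-out) is

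Φ{[(p2−p1)√80 − 1.960·√(2p̄(1−p̄))] / √(p1(1−p1) + p2(1−p2))}.

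| r control / treatment (assumed) | Day-14 rates | Difference, points | Power, 80 per group |
|---|---|---|---|
| 0 / 0 | 61.1% v 91.2% | 30.1 | 99.6% |
| 5% / 5% | 58.1% v 86.6% | 28.6 | 98.6% |
| 10% / 10% | 55.0% v 82.1% | 27.1 | 96.4% |
| 20% / 20% | 48.9% v 72.9% | 24.1 | 88.4% |
| 10% / 20% | 55.0% v 72.9% | 18.0 | 66.0% |

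Worked line, r = 10% in both arms: 0.6111 × 0.9 = 0.550; 0.9118 × 0.9 = 0.821; p̄ = 0.685; (0.2706 × 8.944 − 1.960 × 0.6568)/0.6283 = 1.80; Φ(1.80) = 96.4%.

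With equal relapse among improvers, the day-14 endpoint shows the smaller difference. With more relapse on treatment, it shows a much smaller one, and the first-drop endpoint would not reveal this.

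**The case against.** The strongest reply is that the contradiction is inferred. The protocol nowhere says that a patient who dies after improving is a success; it is silent. The Statistical analysis sentence, with its stated reason of not losing data, may be a last-observation rule for missing data and not a second endpoint. The Abstract's wording is shorthand, and the Discussion's 14-day improvement can equally mean by day 14. Deaths and invasive ventilation are reported as secondary outcomes, level 1 requires demanding discharge criteria, and first improvement within a window is a legitimate endpoint.

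Much of this stands. A reader might infer that the protocol deliberately keeps an early improvement whatever follows, or that its sections flatly contradict each other. The documents support neither: the first is read from silence, and the passages said to conflict each allow another reading. What remains is that the only explicit definition is met by an early improver who later dies, and that the test is binary. Treating the Statistical analysis sentence as a missing-data rule does not supply the absent rule for relapse or death.

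A reader might also infer that the first-drop endpoint costs power, or that it is known to favour the granule. Neither follows. If 20% of day-14 failures in both arms had a passing drop, a true 50% v 70% would appear as 60% v 76% (0.5 + 0.5 × 0.2; 0.7 + 0.3 × 0.2), and power at 80 per group would fall from 74% to 58%. But that model makes relapse among improvers unequal: 10/60 = 16.7% in control against 6/76 = 7.9% on treatment. With equal relapse among improvers the direction reverses, as the working shows. Likewise, 60/80 v 46/80 (p = 0.019) becomes 48/80 v 44/80 (p = 0.52) if 12 and 2 responders relapse, but those counts are invented. They show that the endpoints can disagree, not that they will.

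**Conclusion.** The point holds as a matter of validity. Applied literally, the primary outcome counts as improved a patient who is critical or dead on day 14 after one early drop, and so does not measure the stated aim. The Abstract and Statistical analysis can be read as a day-14 status that would score a surviving relapser differently; the Discussion fits either reading. One definition must be chosen and stated.

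The size cannot be derived from the documents. Under the assumed relapse shares, the difference moves from 30.1 points to between 28.6 and 24.1 with equal relapse of 5% to 20%, and to 18.0 with 10% in control and 20% on treatment. These figures also assume that the planning rates, which the protocol calls a cure rate and then an effective rate, are rates of ever improving.

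**What to change.** Define the primary outcome as alive and at least one point below the baseline status used under Outcomes and measurements, assessed at day 14. Count patients discharged alive as improved unless they are known to have died, or to be back at the baseline level or worse, by day 14. Count any death by day 14 as failure. Report first improvement at any time as a secondary outcome. Use the same definition in the Abstract, Outcomes and measurements, Statistical analysis and Discussion, and say in Statistical analysis whether the final-status sentence is a missing-data rule.

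No new visit is needed, since day 14 is already scheduled, although the status of discharged patients must be known at that point. Response rates will be lower. Power may fall somewhat if improvers relapse equally in both arms: at 80 per group under the planning rates, from 99.6% to 96.4% with an assumed 10% relapse, and to 88.4% with 20%. The change redefines the primary outcome of a trial already recruiting (Trial status), so it needs a protocol amendment and the ethics re-review described under Ethics, and it should be made without knowledge of outcome data by arm.
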